##### Analysis of safety endpoints

- - 1. Clinical laboratory test data will be analysed using appropriate statistical methods, including within-group comparisons before and after treatment, depending on the nature of the variable, and the frequency, incidence, list, detailed time of occurrence, severity, and causal relationship to acupuncture treatment will be reported in graphical form, if necessary. The statistical analysis will be performed by ANOVA, t-test, chi-square or Fisher's exact test, depending on the nature of the variable.
    2. Adverse events: Table all adverse events, categorized by treatment group and body system, with detailed descriptions. For each group, record the frequency of adverse events that are causally related to acupuncture treatment and those that are not causally related. Determine the number of AEs and the proportion of participants experiencing at least one AE within each arm with 95% confidence intervals and compare between arms.
    3. Clinical pathology: Descriptive statistics will be presented for each group and visit for continuous data such as hematology and blood biochemistry test results and vital signs, and differences between visits will be analysed using paired t-test or non-parametric methods.

##### E. Analyzing missing values

1. In the statistical analysis, the validity endpoint is analyzed using the Last Observation Carried Forward (LOCF) method, which substitutes the measurements from the previous equation for any observations that are not observed for any reason, i.e., missing values. For safety evaluation variables, missing values are treated as missing and analyzed.

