#### Test Methods

##### Test design

This study is a randomized, multicenter, parallel design, clinical trial. After receiving sufficient explanation from the researchers involved in this study and voluntarily signing the consent form, participants who are deemed suitable for the study by reviewing the inclusion and exclusion criteria according to the protocol will be assigned a patient identification code. Blood tests will be performed, and they will be randomized to the acupuncture treatment group, electroacupuncture treatment group, and no-treatment control group at a later screening visit.

Each participant will have a screening visit, followed by randomization. If assigned to the acupuncture arm or the electroacupuncture arm, participants will attend bi-weekly visit for a total of 5 weeks, resulting in 10 visits for acupuncture or electroacupuncture, respectively. Subsequently, a follow-up assessment will be conducted 4 weeks later. The control group is required to attend three visits, designated as Visit 1, Visit 10, and Visit 11, respectively.

[figure not shown]

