Sensory, musculoskeletal, endocrine, multiple, urinary, reproductive, digestive, cardiovascular, nervous, dermatologic, and estrogenic systems. Obtain a history of renal, hematologic, lymphologic, respiratory, and other medical and medication history. Any significant findings o n examination at the initial visit should be recorded in the other organ systems section of the case record sheet, and any significant medical findings that meet the definition of an adverse event after initiation of the study procedure should be recorded on the adverse event sheet.

- - - 1. Visual Analog Scale (VAS)

Assess at each visit. At each visit, a VAS for the degree of coldhypersensitivity in the hands and feet will be completed by the participants with the assistance of the investigator.

- - - 1. Pattern Identification Questionnaire and Constitutional Diagnostic Questionnaire (KS- 15)

Administered at Visit 0.

Two principal investigators or a Korean medicine doctor will evaluate the participants.

The evaluator checks the items and marks ◯ on the most appropriate item to indicate the degree of the condition the participant has through the pattern.

The evaluator marks the corresponding pattern identification with a ◯.

- - - 1. Vital signs and height and weight measurements

Vital signs are assessed at every visit. Vital signs include blood pressure, pulse rate, and temperature. Height is measured only at Visit 0, and weight is measured at Visits 0, 10, and 11.

- - - 1. Determining conformance to inclusion/exclusion criteria

At Visit 0, consent, demographic and sociodemographic information, medical and medication history, laboratory tests, pregnancy test and chest x - ray, electrocardiogram, and thermometer measurements to determine if the participant meets the cold diagnostic criteria will be taken.

- - - 1. Check for changes in medical and treatment history

Inquire at each visit whether there have been any changes in medical and treatment history since Visit 0 (Screening). Inquire about any changes compared to what was identified in the drug history screening at Visit 0. If there are any changes in concomitant medications, document them in detail in the case record.

- - - 1. Clinical examination items

Obtain written informed consent and perform a 12-lead EKG, chest x-ray, and examination of the following on Visit 0

①Hematological tests: WBC, RBC, Hemoglobin, Platelet

②Blood biochemical tests: BUN, Creatinine, AST, ALT, r-GTP, Glucose

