6. The acupuncture group and the electroacupuncture group additionally VAS of coldhypersensitivity in the hands and feet at Visit 4 and Visit 8
7. Screening includes hematologic tests (WBC, RBC, Hemoglobin, platelet), blood chemistry tests (BUN, creatinine, AST, ALT, r-GTP, glucose), thyroid function tests (free T4, TSH), urine and urinalysis, and pregnancy test (Urine HCG). At D35 (Visit 10), hematology (WBC, RBC, Hg, platelet), blood chemistry (BUN, creatinine, AST, ALT, r-GTP, glucose) will be performed

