In the acupuncture treatment group and the electroacupuncture treatment group, the next visit will be scheduled within 4±3 days after the treatment, based on the principle of twice-weekly treatment. For the no-treatment control group, the next visit will be scheduled on day 35±3 (visit 10) without any treatment.

##### C. Visit 2 ~ Visit 9

1. Participants dropouts

If a participant violates the protocol for any reason, discontinue participation in the study and record it in the End of Study field. If there is no reason for the violation, the clinical trial proceeds.

Withdrawal from a clinical study is based on the following criteria. Participant will be excluded from the study if any of the following conditions apply, as determined by researcher.

a. Participants will be dropped if predicted treatment adherence is less than 70%. Failure to visit within ±3 days of the scheduled visit will be considered a missed visit.

b. Became pregnant during the study

c. If surgery or hospitalization is required due to a disaster such as an accident or the onset of other diseases

d. In case of refusal by a clinical trial participant

e. Prohibited concomitant medications and therapies.

Example) Anticoagulants, psychotropic medications, antidepressants, medications related to hyperthyroidism, dietary supplements (such as red ginseng), OTC blood flow enhancers, and other medications that may affect coldness in the hands and feet.

f. Worsening of coldness in the hands and feet symptoms requiring standard treatment.

f. Serious adverse events that make it unreasonable to continue in the study.

g. Other unavoidable reasons have arisen that make it impossible to continue the study or that the principal investigator believes would have affected the results of the study.

1. Measure vital signs

Measure and record vital signs.

For vital signs, check and record body temperature, systolic blood pressure, diastolic blood pressure, and pulse rate.

1. Verify medical conditions/medications/treatments (check for changes in medical history and medications)

Check for any new medical conditions, additional medications, or other treatments during Visits 2 through 9.

If so, record it in the Condition/Medical Supplies/Treatment CRF form.

1. General physical exam

Determine if the participant has any of the conditions listed on the general physical examination form in the CRF at the time of the visit.

If present, circle yes and record in the abnormal findings section below.

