#### Statistical Methods

##### General principles

The basic analysis method is the degree of change between the results of the baseline test performed before the clinical trial and the results of the test performed at the end of the clinical trial for the efficacy evaluation indicators, and the significance level is 0.05 by two-sided test.

For the efficacy portion of the study, all data from study participants will be analysed using both an intention-to-treat analysis (ITT), in which all participants who met the inclusion/exclusion criteria and who voluntarily agreed to participate in the human study and were randomized regardless of protocol violations or dropouts, and a per-protocol analysis (PP), in which all participants who were randomized will be included in the analysis, excluding participants with noncompliance or missing data. Missing observations for efficacy endpoints will be analysed using the last observation carried forward (LOCF) method, and missing observations for safety endpoints will be treated as missing.

As assigned analyses include all participants who have completed the baseline and final examinations, with the last examination data considered the final examination data. The safety analysis methodology will also follow the as assigned analysis methodology. As-treated analyses will include patients who completed the final examination with no major protocol violations.

The results of the two analyses should theoretically agree within the same study, but if there is an induced difference between the results, a plausible explanation for the difference should be provided.

For statistical analyses other than those specified in this protocol, please refer to the statistical guidelines for clinical trials.

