##### How to analyze validity variables

- - 1. Primary efficacy endpoint: Visual Analogue Scale (VAS) coldhypersensitivity in the hands and feet

The primary efficacy evaluation variables will be analyzed using the ITT group as the main analysis group, and the results of the PP group will be presented in addition. Repeated ANOVA, paired t-test, etc. will be performed to test whether there is a difference in the change in VAS score between the no-treatment control group and the acupuncture treatment group or the electroacupuncture treatment group. The comparison of the degree of improvement of VAS scores within each group will be performed by paired t-test using the difference between pre- and post- treatment VAS scores (VAS score at Weeks 5±3 days - VAS score at Visit 1).

- - 1. Secondary Validation Variables
       1. Body Temperature (BT; thermometer measurement): Repeated ANOVA is performed to test whether there is a difference in BT change between the acupuncture treatment group and the electroacupuncture treatment group. To compare the degree of improvement in BT within each group, a paired t-test will be performed using the difference between BT before and after acupuncture treatment (BT at Weeks 5±3 days - BT at Visit 1).
       2. WHOQOL-BREF Quality of Life Assessment Questionnaire: ANOVA and post hoc tests will be used to test the difference between each group. Comparison within each group is done by paired t-test using the difference in values before and after acupuncture treatment (value at Weeks 5±3 days - value at Visit 1).
       3. Pattern Identification Questionnaire:
          - This figure shows the distribution of the dialectical observables (dialectical indicators) in participants with coldhypersensitivity in the hands and feet. To determine the relationship between the dialectical indicators and the change in symptom VAS, an ANOVA test (non-parametric test if not normally distributed) and post hoc tests are performed for each indicator with the change in symptom VAS as the dependent variable.
          - Validity and reliability of the basic instrument are evaluated. The validity evaluation is

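### LOCF imputes the primary VAS differently by arm, because controls have no VAS between baseline and Week 5 and the treated arms do

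*Protocol*

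**What the plan says.** The missing-data rule is stated in the protocol itself. Section E, Analyzing missing values, says that "the validity endpoint is analyzed using the Last Observation Carried Forward (LOCF) method". General principles repeats it: "Missing observations for efficacy endpoints will be analysed using the last observation carried forward (LOCF) method". The section on validity variables adds "The primary efficacy evaluation variables will be analyzed using the ITT group as the main analysis group", so dropouts stay in the primary analysis and are imputed. The change score given there is "VAS score at Weeks 5±3 days - VAS score at Visit 1".

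The assessment schedule differs by arm. Under Test design: "The control group is required to attend three visits, designated as Visit 1, Visit 10, and Visit 11, respectively". The Visit 1 section agrees: "For the no-treatment control group, the next visit will be scheduled on day 35±3 (visit 10) without any treatment". Both schedule tables mark the VAS at Visits 2-9 for the treated arms only, and the footnote under Observation and inspection items reads "The acupuncture group and the electroacupuncture group additionally VAS of coldhypersensitivity in the hands and feet at Visit 4 and Visit 8". The Trial Schedule text instead says "At each visit, a VAS for the degree of coldhypersensitivity in the hands and feet will be completed by the participants", and the sections on Visits 2 to 9 and on evaluating validity also read as every visit. These statements need to be reconciled, but on either reading controls have no VAS between Visit 1 and Visit 10.

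The only supplementary efficacy analysis is per-protocol, which leaves out participants with missing data. General principles also describes an as-assigned analysis of those with baseline and final examinations. That does not fit ITT with LOCF, but the primary-endpoint section still puts ITT first.

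**The concern.** One rule produces two different imputations. A control with no Visit 10 score has only the Visit 1 score to carry, so the change is zero by construction. A treated participant who leaves after the first interim VAS carries a partial-treatment change. One who leaves before it is also scored zero.

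The sample-size section plans on a comparator that improves by 0.48, so fixed zeros pull the control mean away from the plan's own expectation. The treated mean is pulled by an amount that depends on when people leave. The two shifts need not cancel, and the primary contrast absorbs the difference.

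Dropout is also unlikely to follow the same pattern in all arms. The trial is open-label with an untreated arm. The 70% adherence rule counts acupuncture sessions, so it can remove only treated participants. Withdrawal for worsening can occur in any arm: a worsening control with no Visit 10 score would be recorded as unchanged, while a worsening treated participant could carry a worsened score.

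**Working it through.** **Inputs.** From the section on number of participants: planning changes of -0.48 (SD 1.03) and -1.52 (SD 1.17), difference 1.04, joint SD 1.102, and 25% dropout in every arm (6 of 24). The -0.48 comes from the placebo arm of an oxygen chamber trial, so using it for an untreated arm is an assumption. The fraction f of the full Week 5 change carried by treated dropouts is not in the documents; it is assumed and varied from 0 to 1.

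**Plan's own figure.** 2 × (1.96 + 0.84)² × 1.102² / 1.04² = 17.61, so 18 per arm, and 18 / (1 - 0.25) = 24. This reproduces the stated 18 and 24. (The printed formula shows 1.17², which would give 19.85; that is a separate matter.)

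**LOCF means at 25% missing.**
- Control: 0.75 × (-0.48) + 0.25 × 0 = -0.36.
- Treated, planning effect: 0.75 × (-1.52) + 0.25 × f × (-1.52) = -1.14 - 0.38f.
- Difference: -0.78 - 0.38f. This equals the true -1.04 only at f = 0.26 / 0.38 = 0.68.
- Treated, no true difference (both arms -0.48): -0.36 - 0.12f, so the false difference is -0.12f.

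| f | LOCF difference (true -1.04) | Relative error | False benefit, no true difference | Type I error |
|---|---|---|---|---|
| 0 | -0.78 | 25% too small | 0 | 0.044 |
| 0.5 | -0.97 | 7% too small | 0.06 | 0.054 |
| 1 | -1.16 | 12% too large | 0.12 | 0.067 |

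The type I error column comes from 50,000 simulated two-sided two-sample t-tests with 24 per arm, SD 1.102 and 6 dropouts per arm. Carried treated values had mean f times the full change and SD 1.102, or were exactly zero at f = 0.

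**Range.** At 10% dropout in each arm the difference runs from -0.936 (f=0) to -1.088 (f=1), and the false benefit is at most 0.048. If untreated controls truly have a mean change of 0, their LOCF mean is 0.75 × 0 = 0 and the control-side bias disappears.

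**The case against.** The strongest reply is that the effect is modest. If treated dropouts carry about half the change, the estimate under equal dropout is slightly conservative and type I error is close to nominal. The per-protocol result is reported beside ITT, any discrepancy must be explained, and a SAP may add sensitivity analyses. The -0.48 is from a placebo arm, so zero is not shown to be wrong for untreated women.

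The point about size stands and sets the severity. The rest does not remove the problem. The per-protocol set drops people with missing data, so it changes the population without testing the imputation in the randomised set. The protocol itself fixes both LOCF and the unequal schedule, so this is not a detail left to the SAP.

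Several stronger readings are tempting but unsupported:
- A reader might quote one-arm dropout: -1.16 if only controls leave, or 0.75 × (-1.52) + 0.48 = -0.66 if only treated participants leave and carry baseline. The protocol plans 25% in every arm, and the second case does not arise from the schedule asymmetry.
- A reader might infer that standard errors are too small. With six controls fixed at zero, the variance of the control mean is about 0.75 × 1.102² / 24 = 0.911 / 24. The usual estimate is about (0.911 + 0.75 × 0.25 × 0.48²) / 24 = 0.954 / 24, slightly larger. Type I error of 0.044 at f = 0 agrees. The issue is the shift in means.
- A reader might extend the point to every comparison and visit. Acupuncture and electroacupuncture share one VAS schedule, and a control missing only Visit 11 carries Visit 10, not baseline.

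**Conclusion.** The concern holds for the Week 5 comparison of each treated arm with control. The same rule scores a missing control as no change and a treated dropout with an interim VAS at an on-treatment value. On the planning figures this moves the estimate by between 0.26 points towards zero and 0.12 points away from it. No direction can be claimed in advance, because it depends on who leaves and when. With no true difference and equal dropout, any bias favours treatment, by at most 0.12 points. These sizes rest on 25% dropout in every arm, an untreated change of -0.48 borrowed from a placebo arm, and an assumed f. This should be fixed before analysis, but it does not by itself invalidate the trial.

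**What to change.** Replace LOCF as the primary rule with a baseline-adjusted analysis under missing-at-random. Either use a mixed model on Visits 1, 10 and 11, which all arms share, or ANCOVA with multiple imputation by arm that uses baseline and, in the treated arms, the interim VAS.

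Add a delta or tipping-point sensitivity analysis that shifts the imputed values in each arm separately, controls included. Control-based imputation alone would not be enough: it alters only treated dropouts and leaves the missing controls untested. Keep LOCF as a sensitivity analysis at most. Reconcile the Visit 4 and 8 footnote with the every-visit text, so that the interim data available for imputation are known.

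The cost is protocol and SAP wording and a little programming, with no extra visits or participants. The drawback is reliance on missing-at-random, which for controls rests on baseline and any Visit 11 score; the separate shifts are there to test it.

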#### Handling of adherence and protocol violations in clinical trials

- 1. The principal investigator and personnel in charge of this study must be fully familiar with and thoroughly implement the protocol to prevent violations of the protocol from occurring. On the other hand, any unavoidable violation of the protocol shall be handled as follows.
  2. In the case of serious violations, e.g., violation of inclusion/exclusion criteria, failure to obtain informed consent, etc. that may have a significant impact on the safety and outcome of the study, the participant shall be dropped out of t h e study.
  3. For other minor violations, accurately describe the extent of the violation or delay and the reason for it, and consider whether it affected the pilot study when analysing the results.

#### Resource Management

The principal investigator will manage the data from this study in a manner that maintains objectivity, safety, and complementarity, in accordance with the procedures below. Upon completion of this study, data specific to this study will be kept in a separate file for 3 years.

##### A. Check case notes and raw data

The Case Record Form (CRF) should be filled out as soon as the data to be recorded occurs. If it is not recorded by the end of the case, the appropriate reason for the missing data should be recorded. All amendments should be marked by crossing out the original record and recording the amendment, the amender, the reason for the amendment, and the date of the amendment. Do not use a redaction that obscures the original record.

The CRFs of the patients whose case records have been completed are delivered to the computerized data entry personnel at the race track clinical trial site for entry into the computerized system through the source document verification process as stipulated in the SOP of the organization to which the separate monitoring personnel belong. After all data are entered into the computerized system, the source documents and CRFs shall be kept so that they can be verified upon request by relevant government agencies, sponsors, etc.

The investigator should provide normal ranges and reference values in an appropriate location, such as the CRF, before the trial begins so that the computerized record can be used for verification or validation.

#### Informed consent form

In conducting this study, after fully explaining the contents of this study, the effect of electroacupuncture treatment, acupuncture treatment and adverse events to the participants in advance, the participant's consent is obtained and the consent form is completed, and the date of obtaining consent is recorded in the case record.

#### Protocol for victim compensation

Attachments

#### Standards of care and treatment for post-trial research participants (proposal)

Seek medical attention for adverse events requiring treatment or for participants requiring ongoing treatment.

#### Measures to protect the safety of human participants and etc.

- 1. Pre-treatment testing will be performed to strictly evaluate whether the participant is appropriate for this study.
  2. For any adverse event that appears to be related to the study, the principal investigator shall immediately notify the Institutional Review Board and follow its instructions. However, in cases requiring emergency medical treatment, it is the responsibility of the principal investigator to reprot after preliminary treatment.
  3. Consider all possibilities that may involve a risk of physical injury (including any side effects that affect the body, such as rashes, infections, etc.).
  4. If a participant receives medical treatment for physical injuries that occur as a direct result of participant's participation in the study (and that are not normally expected in the ordinary course of medical care), the participant will not pay for the treatment.
  5. The medical expenses for physical damage caused by the research commissioned by Sangji University Industry-Academic Cooperation Center shall be paid by the insurance company subscribed for this research unless the researcher is grossly negligent due to intentional or negligent acts.
  6. During the study, participants will be treated with traditional chinese medicine for coldhypersensitivity in the hands and feet if their symptom worsen. Since there is no standardized treatment for coldhypersensitivity in the hands and feet, the treatment will be based on the existing treatment methods in korean medicine.

